**B) Hypotheses:**

Psoriasis is mediated through a type-1 pathway that can be affected by blocking CD11a.

1. CD11a blockade correlates with suppression of Type 1 inflammatory gene products;
2. Functional blockade of T-cell activation will persist only while LFA-1 is blocked/ down-regulated by Efalizumab.
3. T-cell activation through TCR complex will be blocked by efalizumab
4. Efalizumab decreases VLA-4 expression and this will have the functional consequence of blocking cell adhesion to fibronectin (a VLA-4 ligand).
5. **Aim:**

Primary:

- To determine whether improvement of target plaque under therapy with Efalizumab is correlated with changes in expression of defined inflammatory genes in the target plaque, and to characterize the contribution of defined inflammatory genes to the overall psoriatic inflammation process at different time points.

Secondary:

- To assess the correlation between functional CD11a blockade and response to treatment.
- To determine the mechanism of action of efalizumab in psoriasis focusing on blockade of important surface proteins during immune synapse formation (including TCR, LFA-1, VLA-4).
- To determine alterations of circulating leukocytes during and after efalizumab treatment.

1. **Primary outcomes:**
2. Clinical improvement of target lesions as measured by the **“Clinical Response Score”,** a single composite score based on quantitative measurement of epidermal acanthosis, qualitative expression of Keratin16 (histochemistry assessment) and quantitative measurement of K16 mRNA.
3. Measure genomic modulation by efalizumab real time RT-PCR for a set of pre-defined disease associated genes.
4. Characterization of inflammation through integration of quantitative expression of mRNAs encoding IL-12, gamma-interferon, STAT1, iNOS and IL-8 into the **“Type 1 pathway score”** (composite score derived by a novel multivariate analysis program).
5. Measure broad genomic modulation of psoriatic genes on the mRNA level using Affymetrix arrays in conjunction with cluster analysis programs at baseline and day 84 in circulating leukocytes and cells within psoriatic skin lesions.
6. **Secondary outcomes:**

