This is an open-label study to investigate the mechanism of action of efalizumab (anti-CD11a). After a wash-out period from standard therapies, patients with moderate to severe psoriasis will be treated with subcutaneous injection of 1.0 mg/kg/week efalizumab for 24 weeks.

- Patients will be assessed by the PASI score and a modified, “linear PASI score”. Patients will also be categorized as “*responders*” and “*non-responders*” according to objective outcome criteria (**Clinical Response Score** and **Type-1 Pathway Score**). The primary goal is to study the cellular and genomic basis for therapeutic improvement or resistance to CD11a blockade.

At baseline, an index plaque will be selected for serial biopsy analysis. This plaque is located on the trunk, buttocks, or thigh (sensitive areas such as the face will not be biopsied). Punch biopsies will be performed from the index plaque at baseline (before treatment) and after 2, 6 and 12 weeks of treatment with efalizumab. The response to treatment at 12 weeks will be graded. Complete responders according to the **Clinical Response Score** will be defined as patients that reverse keratin 16 expression in conjunction with reversed acanthosis and normalized differentiation. The clinical responses will be graded from best to worst using a multivariate analysis technique that creates the “**Clinical Response Score**” based on a combination of epidermal thickness, the qualitative pattern of keratin 16 expression, and quantitative expression of keratin 16 mRNA. The stratification of clinical responses by this technique provides a measure of disease improvement that can be subsequently related to quantitative alterations in expression of other disease-related and inflammation-related genes.

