The impact of CD11a blockade on a functionally linked pathway of inflammatory genes will be measured by the **Type-1 Pathway Score**. The genes included in this pathway are central to the activation of type 1 T-cells (IL-12, -IFN) and to genes regulating downstream inflammation (STAT1, IL-8, iNOS, MIG, etc). Because multiple genes are multiple independent variables, the **Type-1 Pathway Score** will serve as a novel multivariate analysis scoring tool. This allows us to compare “clinical” response outcomes **(Clinical Response Scores**) to modulation of type 1 inflammation-related genes **(Type-1 Pathway Score**). We will study the extent to which a response outcome is related to the number of residual T-cells in treated lesions versus the quantitative levels of -IFN mRNA (a direct measure of T-cell activation in plaques).

- Broad gene expression analysis in psoriatic skin lesions and blood at baseline, at the primary study endpoint (12 weeks of treatment) will be performed using a combination of gene arrays and real-time RT-PCR techniques.
- Cellular mechanisms associated with reductions in activation-controlling surface proteins on circulating and lesional T cells before and during efalizumab treatment will be studied. Previous work showed that T-cell activation is significantly impacted by efalizumab and several activation-controlling surface proteins are down-regulated during active treatment. Peripheral blood T-lymphocytes will be analysed at baseline, week 12 and in 2 week intervals after the last dose of efalizumab. This will include an analysis of dendritic cells in the peripheral circulation.
- Preliminary data demonstrated that VLA-4, an integrin unrelated to LFA-1, was down-regulated by efalizumab. Here, we will explore the functional consequences of VLA-4 modulation by efalizumab using functional binding assays with fibronectin as a ligand. We will determine whether this alteration is caused by reduced synthesis of VLA-4 or altered intracellular trafficking of integrin molecules. This will be in conjuction with [name] laboratory.
- Phenotype of cell suspensions of shave biopsies will be determined at baseline, week 2 and week 12, particularly to classify DC populations.

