**APPENDIX F**

**Research Blood Tests**

1. **IMMUNOHISTOCHEMISTRY AND IMAGE ANALYSIS**

Tissue sections will be stained with haematoxylin and eosin (H&E) and with purified mouse anti-human monoclonal antibodies to K16, CD3, CD8 and CD103. Biotin-labeled horse anti-mouse antibody will be used for amplification, with avidin-biotin complex and developed with chromogen 3-amino-9-ethylcarbazole. Epidermal thickness measures will be computed using National Institute of Health software (NIH Image 6.1), and positive cells will be counted manually using computer-assisted image analysis. Conformational states of LFA-1 will be analyzed where there are suitable antibodies available for immunohistochemistry.

1. **RT-PCR ANALYSIS**

The PAXgene Blood RNA System is a commercially available integrated and standardized system for the collection and stabiization of whole blood specimens and isolation of cellular RNA. As an alternative, CPT tubes may also be used for this purpose. We will collect blood samples at time points indicated in Appendix I. Genes of interest include inflammatory genes and those responsible for the phenotype of psoriasis (-IFN, TNF-, STAT-1, iNOS, IL-8, MIG, IP-10, IL-19, IL-20, IL-23); those representative of T-cell activation (IFN-, IL-12, CD25); dendritic cell activation (CD80, IL-12); keratinocyte proliferation (Keratin 16); Type 1 or Type 2 T-cell immune deviation (-IFN , IL-4, IL-10, IL-11) and new genes discovered from gene chip data (ENRAGE, MMP). Other genes may be studied as they are discovered or their relevance is newly appreciated.

RNA will be extracted from tissues frozen in liquid nitrogen using the RNeasy Mini Kit. The primers and probes for the TaqMan RT-PCR assays for chosen genes have been generated using the Primer Express algorithm, version 1.0, using published genetic sequences (NCBI-PubMed) for each gene. The RT-PCR reaction will be performed using EZ PCR Core Reagents according to the manufacturer's directions. The samples will be amplified and quantified on an Applied Biosystems PRISM 7700 using the following thermal cycler conditions: 2 min @ 50C; 30 min @ 60 C; 5 min @ 95C; and 40 cycles of 15 sec @ 95C followed by 60 sec @ 60C. The human acidic ribosomal protein (hARP) gene, a housekeeping gene, will be used to normalize each sample and each gene. The data will be analyzed and samples quantitated by the software provided with the Applied Biosystems PRISM 7700 (Sequence Detection Systems, ver.1.7).

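### The synopsis puts the Type-1 Pathway Score into the responder label, against the rest of the protocol; a test of that score between groups so labelled would be circular

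*Protocol*

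**What the plan says.** All references are to the protocol; no SAP is at hand.

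- **Synopsis, responder categories.** Patients are to be labelled responders or non-responders "according to objective outcome criteria (Clinical Response Score and Type-1 Pathway Score". No cut-off and no combination rule is given. The sentence that follows makes the cellular and genomic basis of improvement or resistance the main goal.
- **Synopsis, next paragraph.** Responses are graded by the Clinical Response Score alone, "based on a combination of epidermal thickness, the qualitative pattern of keratin 16 expression, and quantitative expression of keratin 16 mRNA". Complete responders are defined by reversal of keratin 16 and acanthosis with normal differentiation. The grading is afterwards to be related to other disease and inflammation genes.
- **Synopsis, Type-1 Pathway Score.** Clinical Response Scores are to be compared "to modulation of type 1 inflammation-related genes", so the two scores stand on opposite sides of the comparison.
- **Primary aim.** "To determine whether improvement of target plaque under therapy with Efalizumab is correlated with changes in expression of defined inflammatory genes".
- **Primary outcomes.** The Clinical Response Score is a "composite score based on quantitative measurement of epidermal acanthosis, qualitative expression of Keratin16 (histochemistry assessment) and quantitative measurement of K16 mRNA". The Type-1 Pathway Score is the "integration of quantitative expression of mRNAs encoding IL-12, gamma-interferon, STAT1, iNOS and IL-8 into the" composite. The two lists share no component.
- **Statistical Model.** In the pilot, response came from K16 mRNA and epidermal thickness. Four patients with a positive response score were compared with five with a negative one on the pathway score. The resulting statistic of 6.102 on 1 degree of freedom is the basis of the sample size.

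**The concern.** The pathway score is the variable whose link with response is under study. If it also helps decide who counts as a responder, responders will have more favourable pathway scores whether or not type-1 gene suppression has anything to do with clinical improvement. A significant difference between the groups would then say nothing about mechanism.

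The wording matters because this is the only sentence that states how this trial's patients receive the two labels. The Statistical Model describes how the pilot patients were grouped, and the later definition in the synopsis covers complete responders only. In an open-label study of about 30 patients with no stated combination rule, an analyst could follow the synopsis sentence in good faith, and the rule could be settled after the pathway data are known.

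**Working it through.** **1. What the study is sized on.** The Statistical Model takes the pilot statistic 6.102 from 9 informative patients, a required non-centrality of 14.37, and a factor of 1.25 for uninformative patients:

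14.37 / 6.102 × 9 × 1.25 = 26.49, rounded up to 27; 27 / 0.90 = 30 enrolled.

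The plan's figures reproduce from its own expression. (The 14.37 is not the value for 95% power at two-sided 5%, which is (1.960 + 1.645)² = 12.99. That is a separate matter and does not affect this point.) What matters here is the test behind 6.102: groups formed by the sign of the response score, with the pathway score as the tested variable.

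**2. The definitions side by side.**

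| Place in protocol | What defines response | Pathway genes included? |
|---|---|---|
| Synopsis, responder categories | Clinical Response Score and Type-1 Pathway Score | Yes |
| Synopsis, next paragraph | Thickness, K16 pattern, K16 mRNA | No |
| Synopsis, pathway score | Clinical Response Score, set against the pathway score | No |
| Primary outcomes | Acanthosis, K16 staining, K16 mRNA | No |
| Statistical Model (pilot) | K16 mRNA and epidermal thickness | No |

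The first row stands alone against the other four.

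**3. Why the label drives the result.** Suppose the two scores are independent and each is favourable in half of the patients.

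- Both must be favourable: all responders have a favourable pathway score. Among non-responders the share is (1/4) / (3/4) = 1/3.
- Either may be favourable: the share among responders is (1/2) / (3/4) = 2/3, and among non-responders it is 0.

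The groups differ on the tested variable with no association present.

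**4. Size of the effect.** Simulation under no association:

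- Three response variables and five pathway variables, normal, generated independently of each other, with correlation 0.5 or 0.7 within each set.
- Scores computed by the pairwise rule in the Statistical Model.
- Mann-Whitney test of the pathway score between groups at two-sided 5%.
- 2,000 runs per setting; at least 1,997 gave two usable groups.

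| n, within-set correlation | Clinical Response Score > 0 only | Both > 0 | Either > 0 | Sum of standardised scores > 0 |
|---|---|---|---|---|
| 27, 0.5 | 4.8% | 81.1% | 81.7% | 89.6% |
| 27, 0.7 | 4.4% | 80.9% | 81.1% | 92.0% |
| 30, 0.5 | 4.6% | 85.7% | 86.0% | 92.2% |
| 30, 0.7 | 5.0% | 86.6% | 87.9% | 94.7% |

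A simpler check with two independent scores (n = 27, 4,000 runs, Wilcoxon test) agrees: 78.4% when both must be favourable, 90.7% on the sum, and 4.5% with the Clinical Response Score alone.

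**The case against.** The strongest reply is that the synopsis sentence is a one-line overview and not an analysis definition. Each place that describes the primary comparison keeps the two scores apart, and the two composites have no component in common. The synopsis sentence does not say that its categories will be used to test the pathway score. The high false-positive rates depend on combination rules that appear nowhere in the protocol. Under the grouping the Statistical Model describes, the rate is about 5%.

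Most of this stands, and it limits the finding in two ways.

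- A reader might infer that the primary comparison is circular as planned. The documents do not support that: the comparison that is described and sized uses a response score without pathway genes.
- A reader might infer that every responder versus non-responder comparison is circular. That does not follow either. The secondary outcome on surface molecules and activatability of lesional T cells concerns variables outside the pathway score. Its grouping label would be contaminated, but the difference would not arise by construction.

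A reader might also suspect a built-in link because K16 mRNA and the cytokine genes are normalised to the same housekeeping gene (Appendix F, RT-PCR analysis). That is a described assay step and not an error in the plan. Any effect would depend on a measurement-error size that the documents do not give, so it is no part of this finding.

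The reply does not remove the contradiction. The synopsis sentence is explicit, and nothing in the protocol says that the Statistical Model's pilot grouping overrides it.

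**Conclusion.** The point holds as an internal contradiction with a serious conditional consequence. The synopsis includes the Type-1 Pathway Score in the responder label, while the rest of the protocol builds response without it. If the synopsis categories are used for the two-group test of the pathway score, that test is circular, with false positives of about 80% to 95% at a nominal 5%. If groups are formed from the Clinical Response Score alone, the rate stays at about 5%.

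The 80% to 95% range rests on assumptions that are not in the documents: normal data, within-set correlations of 0.5 or 0.7, and three possible combination rules, since the protocol states none. Every rule tried gave roughly 80% or more, so the conclusion does not depend on which is chosen. The range is not the error rate of the primary analysis as the Statistical Model describes it.

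**What to change.** In the synopsis sentence on responder categories, delete the reference to the Type-1 Pathway Score. Define responders by the Clinical Response Score alone, with a cut-off fixed in advance; its sign, as in the pilot analysis in the Statistical Model, would do. State that the Type-1 Pathway Score serves only as the variable under test. Use the same label for the secondary responder versus non-responder comparisons.

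The cost is one phrase removed and one cut-off stated. No patient, visit, biopsy or assay is added, and the sample size is unaffected because it already rests on groups formed by the response score. Repeating the primary association with K16 mRNA left out of the response score is at most an optional sensitivity analysis and is not needed to resolve this point.

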Effects of efalizumab on psoriasis disease activity, infiltration of skin lesions by T-cells (and other leukocytes), and expression of inflammation-related genes was assessed in skin biopsies obtained from 13 patients in the MOA sub-study. Six of 13 patients were judged to have a good response to efalizumab based on decreased epidermal hyperplasia and elimination of keratin 16 immunostaining in week 8 biopsies. On average, T-cells were reduced about 50% in week 8 biopsies from skin lesions. Quantitative RT-PCR measures of disease-related or inflammation-related genes showed consistent reductions in K16, IL-12 p40, -interferon, STAT-1, IL-8, and iNOS in good responders (by the histologic definition of response). Quantitative suppression of inflammation-related genes correlated better with response status than quantitative reductions in T-cells within lesions. To the extent that the group of inflammation-related genes forms a functionally-linked pathway, all measures were grouped into a "pathway score" according to a multivariate statistical method developed by [name]. By the same techniques, a composite clinical response score was constructed using a combination of histologic response measures and K16 gene expression. Composite clinical responses were much more highly correlated with an inflammation pathway score compared to a T-cell infiltration score.

Our overall analysis of results obtained with peripheral blood T-cells and psoriatic skin lesions suggests that one of the most important mechanistic effects of efalizumab may be suppression of T-cell activation, leading to decreased production of -interferon and other inflammatory products regulated downstream by -interferon/STAT1. As this view would significantly alter the current hypothesis that efalizumab improves psoriasis mainly by reducing T-cell trafficking into inflammatory skin sites, our new hypothesis would be significantly strengthened through the study of additional patients. In addition, the study of new patients would provide the opportunity to explore the mechanism by which T-cell activation is broadly affected by relatively selective targeting of a single cell surface integrin.

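### Whole-tissue gamma-interferon mRNA is labelled a direct measure of lesional T-cell activation, but it also moves with T-cell number, so on its own it does not favour activation over trafficking

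*Protocol*

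**What the plan says.** Under Preliminary Findings from Mechanistic Studies, the Protocol reports from the pilot: "On average, T-cells were reduced about 50% in week 8 biopsies from skin lesions". It proposes suppressed T-cell activation as a new hypothesis, against the current view that "efalizumab improves psoriasis mainly by reducing T-cell trafficking into inflammatory skin sites".

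The Synopsis and brief description of the study carries this into the new trial. In the paragraph on the Type-1 Pathway Score, response is to be related to the "number of residual T-cells in treated lesions versus the quantitative levels of" gamma-interferon "mRNA (a direct measure of T-cell activation in plaques").

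Appendix F (RT-PCR analysis) gives the method for skin: "RNA will be extracted from tissues frozen in liquid nitrogen using the RNeasy Mini Kit". On normalisation it says: "The human acidic ribosomal protein (hARP) gene, a housekeeping gene, will be used to normalize each sample and each gene". No T-cell denominator is stated. The same appendix (immunohistochemistry and image analysis) stains sections for CD3 and CD8, and "positive cells will be counted manually using computer-assisted image analysis".

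Two other parts bear on the point. The primary outcomes build the Type-1 Pathway Score from five genes, of which gamma-interferon is one. The secondary outcomes explore the activatability of lesional T-cells in responders and non-responders.

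**The concern.** The label decides the interpretation before the data are seen. A whole-tissue mRNA level normalised to a gene that is not specific to T-cells depends on T-cell number as well as on expression per T-cell. T-cell number is the other side of the planned contrast, so the two measures share the trafficking component.

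If response followed T-cell number alone, gamma-interferon mRNA would still correlate with response. With the label in place, that correlation would read as support for activation blockade, which is the new hypothesis. Which measure correlated better would depend partly on which was measured with less error.

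**Working it through.** **Inputs from the Protocol.** T-cells down about 50% at week 8 (Preliminary Findings). RNA from whole frozen tissue, normalised to hARP (Appendix F). Number of patients from the Statistical Model: 14.37/6.102 × 9 × 1.25 = 26.49, so 27; 27/0.9 = 30 enrolled. Both figures reproduce, and 27 is used below. The point itself rests on no figure stated in the plan.

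**Step 1: arithmetic.** Assume hARP is constant, T-cells are the only source and all T-cells express equally. Then bulk level = T-cell number × expression per T-cell.

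| T-cell number | Expression per cell | Bulk level | Bulk ÷ number |
|---|---|---|---|
| ×0.5 | ×1.0 | ×0.5 | ×1.0 |
| ×1.0 | ×0.5 | ×0.5 | ×0.5 |

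Pure trafficking and pure activation give the same bulk level. They separate only after division by T-cell number.

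**Step 2: size at n = 27.** On the log scale let N be T-cell number (SD 0.7), A expression per cell (SD 0.35 or 0.7), C = N + counting error (SD 0, 0.35 or 0.7), I = N + A + PCR error (SD 0.3), and index = I − C. The outcome is coded so that higher means more residual disease. It equals N plus noise (SD 0.7) under pure trafficking and A plus noise (SD 0.7) under pure activation. All SDs are assumptions. There were 3,000 runs per scenario, using Spearman correlations at the two-sided 5% level; the last column is a linear regression. Each cell shows the results for per-cell SD 0.35 / 0.7.

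| Truth | Count error SD | r, bulk | Bulk significant | r, count | Bulk beats count | Index significant | Bulk significant, adjusted for count |
|---|---|---|---|---|---|---|---|
| Trafficking | 0 | 0.551 / 0.442 | 87.3 / 67.1% | 0.670 / 0.667 | 11.8 / 4.9% | 4.9 / 5.4% | 5.4 / 5.3% |
| Trafficking | 0.35 | 0.558 / 0.446 | 88.9 / 67.7% | 0.596 / 0.594 | 38.9 / 17.2% | 4.9 / 4.8% | 20.8 / 11.9% |
| Trafficking | 0.7 | 0.555 / 0.444 | 88.3 / 67.0% | 0.465 / 0.467 | 70.9 / 45.0% | 4.7 / 4.6% | 59.6 / 34.2% |
| Activation | 0 | 0.173 / 0.449 | 14.2 / 69.0% | 0.002 / −0.001 | 92.5 / 99.8% | 37.9 / 94.9% | 40.2 / 96.9% |
| Activation | 0.35 | 0.170 / 0.449 | 13.6 / 68.3% | 0.004 / 0.001 | 87.0 / 99.7% | 24.1 / 87.4% | 27.9 / 93.1% |
| Activation | 0.7 | 0.174 / 0.447 | 14.9 / 67.9% | 0.001 / 0.002 | 82.7 / 99.0% | 14.8 / 67.2% | 21.0 / 83.8% |

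Under pure trafficking, bulk gamma-interferon is significant in 67 to 89% of runs. As counting error grows it beats the count in up to 71%. Adjusting for a noisy count by regression does not remove the problem: it still rejects in up to 60%.

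**Step 3: other assumed SDs.** With T-cell SD 1, a response correlation of about 0.6, counting error 0.3 to 1.0, per-cell variation 0.3 to 1.0 and PCR error 0.3, pure trafficking gives bulk significant in 56 to 84%, bulk beating the count in 16 to 78%, and the index significant in 5 to 6%. The count is significant in 56 to 89% under trafficking and in 4 to 6% under activation.

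**Step 4: where the index fails.** If gamma-interferon rises with T-cell number at log-log slope b, the index equals (b − 1)N + A + errors. Only b = 1 removes N. With b = 0.5 under pure trafficking and the SDs of step 3, the index has a false negative correlation with the outcome (r = −0.18 to −0.38) that is significant in 14 to 55% of trials. That sign is opposite to what activation predicts. A slope above 1 would give the same sign as activation.

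**The case against.** A reader might infer that the design cannot separate activation from trafficking at all. The documents do not support that. T-cell number is the other arm of the contrast and is counted on sections. In the simulations the count correlates with response under trafficking (about 0.47 to 0.67) and not under activation (about 0.00), so the pair of correlations does carry information. The secondary outcomes explore lesional T-cell activatability and plan in vitro activation assays on T-cells.

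A reader might also infer that a trafficking effect would necessarily be reported as activation blockade. The Protocol states no rule that a gamma-interferon correlation proves activation, and the form of the joint analysis may properly sit in an SAP that is not shown.

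The pilot does not show the feared pattern either. In the Statistical Model, gamma-interferon correlates at only 0.18 with response, the lowest of the five genes, against 0.52 for epidermal and 0.12 for dermal CD3+ cells. With 12 patients this settles little: by Fisher's z the 95% interval for 0.18 runs from −0.44 to 0.68.

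Finally, a ratio is no cure-all. It assumes proportionality (step 4). Under activation it does about as well as bulk mRNA when counting error is large (14.8 against 14.9%, and 67.2 against 67.9%, at SD 0.7).

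All of this limits the point. None of it makes the label correct, and the label is Protocol text, not a detail deferred to an SAP.

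**Conclusion.** The label is wrong by the Protocol's own assay method. hARP-normalised whole-tissue gamma-interferon mRNA reflects T-cell number as well as expression per T-cell. Neither its correlation with response nor its outperforming the T-cell count favours activation over trafficking by itself. Under pure trafficking at n = 27, bulk mRNA is significant in 56 to 89% of simulated trials across both sets of assumptions, against about 5% for a per-T-cell index.

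These percentages rest on assumed SDs, on proportional scaling and on T-cells as the only source. The direction of the argument needs only that gamma-interferon mRNA rises with T-cell number. The error is confined to one statement and one comparison: the study as a whole can still address the question, and the five-gene score stands.

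**What to change.** In the Synopsis:

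- Delete the direct-measure wording and describe bulk gamma-interferon mRNA as a measure of overall lesional type-1 inflammation.
- Add a T-cell-normalised index: gamma-interferon mRNA per CD3+ count from the same biopsy, or per CD3 mRNA from the same extract.
- Claim support for activation over trafficking only when the T-cell count, the bulk level and the index are read together, with the index related to response in the direction that activation predicts. Do not rest the claim on bulk mRNA alone, on regression adjusted for a noisy count, or on the ratio alone.
- Check proportionality on baseline biopsies and state it as a limitation. Counting error alone flattens the observed slope: with T-cell SD 0.7 and error SD 0.7, a true slope of 1 appears as 0.49/(0.49 + 0.49) = 0.5.

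Cost: Protocol wording. CD3 staining and counting are already planned, and CD3 mRNA would need one further primer-probe set. The index is noisy, so support for activation becomes harder to earn.
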